### Secondary outcomes

**Psychological assessments:** We will administer standard questionnaires, valid for Indian adults/adolescents for psychological measures of chronic stress and behavioural assessment.

1)
Perceived stress scale
^1^, a commonly used 14-item scale to measure the degree to which situations in one’s life during the past month are appraised as stressful, and gives a measure of chronic stress.

2) Stressful Life Events Scale is a 40-item scale to assess chronic stress caused by life events among participants in the past one year
^42^.

3)
Strengths and Difficulties Questionnaire, a behavioural screening questionnaire for children and adolescents.

4) Depression and other psychological health issues will be identified using the Patient Health Questionnaire-9 (PHQ-9) and MINI (Mini International Neuropsychiatric Interview)
^43,
44^. The
PHQ-9 is a screening questionnaire for depression, and gives a score that measures severity of depression, while MINI is a diagnostic interview schedule for diagnosing depression.

5) Cognitive function will be assessed in Mysore, and Pune (as part of ongoing follow-up), using Wechsler Adult Intelligence Scale-Fourth Edition - India (WAIS-IV
^India^) a widely used standard IQ test designed to measure intelligence and cognitive ability in adults and older adolescents
^45^. In Mumbai, cognitive function has been recently assessed for the SARAS KIDS children using three core tests from the Kauffman’s Assessment Battery and some additional tests
^46–
48^.

**Cardiometabolic assessments:** We will measure weight (digital scale), height (adult stadiometer), head, mid-upper arm, waist and hip circumferences (anthropometric tape), subscapular and triceps skinfold thickness (Harpenden callipers), hand-grip strength (Jamar dynamometer), and body composition (bioimpedance). Waist-to-hip ratio will be calculated for central adiposity. Resting blood pressure will be measured on the non-dominant arm using an automatic device after the participants have been seated relaxed for five minutes.

An oral glucose tolerance test (
WHO protocol) will be administered in Mysore after an overnight fasting for plasma glucose, insulin and lipid concentrations. In Mumbai and Pune OGTTs using the WHO protocol have been carried out recently as part of ongoing follow-up.

**Lifestyle indicators:** Dietary intake will be assessed using a purpose-designed food frequency questionnaire (FFQ)
^49^ and a 24-hour recall questionnaire (
Supplementary File 1 and
Supplementary File 2). Physical activity will be measured using the
International Physical Activity Questionnaire – Short version. Information on smoking and alcohol intake will be documented. 

**Laboratory assays:** All assays will be carried out using standard protocols. Salivary samples for cortisol assay will be collected using synthetic swabs (Salivette
^®^Cortisol, Sarsteadt, Germany). Samples will be stored at -20° till analysis.

A part of the whole blood sample at all time points (EDTA vacutainer) will be transferred to 2 ml micro centrifuge tubes for a hemogram. The remaining blood will be centrifuged (2500 g × 15 min) within 30-minutes of collection, and the separated plasma stored at -80°C until further analysis. Packed cells will be stored for DNA.

Biochemistry analyses will be undertaken for various measurements:

• Hemogram: Cell Counter hematology analyser on the day of collection.• Plasma glucose and lipids: Automated biochemistry analyser (Hitachi 902, Roche Diagnostics, Germany) using standard enzymatic kits.• Insulin: ELISA kit (Mercodia AB, Uppsala, Sweden).• Cortisol: ELISA kit (Alpco Diagnostics, Salem, NH)

**Epigenetic assays:** In the Parthenon and SARAS KIDS cohorts, we will use a candidate gene approach to assess epigenetic characteristics (DNA methylation) at the gluco-corticoid receptor (
*NR3C1*) and
*11β-HSD2* gene loci in relation to maternal factors and offspring stress responses, and explore the effect of maternal nutritional supplementation on these associations. Studies in humans and animals have shown that methylation levels in the promoter regions of these genes may be influenced by maternal GDM and/or undernutrition and have adverse implications for offspring stress responses
^50–
52^.

**Neuroimaging:** We will collect the following Magnetic Resonance Imaging (MRI) biomarkers in subsamples of participants in Mysore and Mumbai (N=100 each): 1) whole brain, hippocampal and amygdale volumes and cortical thickness and surface area, 2) cortical structural complexity measured using fractal dimension from volumetric images, 3) white matter integrity quantified by fractional anisotropy, radial diffusivity and mean diffusivity from diffusion tensor imaging and 4) functional connectivity of networks quantified from resting state fMRI.

T1-weighted volumetric sequences will be acquired for the assessment of brain regional volumes, cortical thickness, cortical surface area, gyrification index, fractal dimension, voxel base morphometry analysis.

Neuroimaging data will be investigated with the aim of identifying significant correlations of cortisol and cardiovascular stress responses with structural and functional brain networks.

**Other:** Information will be collected on medical and drug history, recent stressful events, education, occupation and socio-economic status, and parental diabetes and cardiovascular disease.

### Intervention development

We propose to develop a socio-cognitive intervention method for stress management. We intend to use a person-based approach to develop a culturally-appropriate intervention design within the overarching framework of the MRC guidance on complex intervention development
^53,
54^. ‘A person-based approach to intervention development’ aims to understand, and accommodate, the perspectives and psychosocial context of the intervention users in a systematic manner, through qualitative research, thus strengthening evidence-based interventions.

We will carry out three distinct pieces of work that will run parallel with the other components as below.

**i) Systematic review:** will be carried out to understand what works in reducing perceived stress in adolescents and young adults. We will follow the Preferred Reporting Items for Systematic Reviews and Meta-Analyses (
PRISMA) statement
^55^.

Eligibility criteria, search strategy and identification of literature: We will consider any non-therapeutic psychological interventions as our exposure of interest. Outcome will be ‘perceived stress’ in adolescents and young adults. We will include all intervention studies published in English until the start of the review process. We will search Medline/PubMed and the Cochrane Library databases using the medical subject headings (MeSH) terms and text word terms and reference lists of retrieved literature.

Data extraction and quality assessment: Data extraction and quality assessment of each article will be carried out independently by [name] and another assessor. Discrepancies between assessors will be resolved by discussion with a third independent assessor.

Evidence synthesised from this will inform the content and delivery form of the intervention.

**ii) Formative qualitative research**: We will conduct qualitative interviews with ~25 adolescents and young adults in Mysore, soliciting their views on stresses and stressors that affect their daily life, and the ways to tackle them. Specific suggestions from the participants for activities and techniques to be used in the intervention design will be discussed (eg. digital sources of support). Analysis of the pooled data from this work will identify ‘guiding principles’ on the key issues that must be addressed by the intervention, and specific ideas about the most effective types of support that could be offered.

**iii) Development of intervention format and content:** This work will produce 1) a co-created set of intervention materials that are ready to be tested, and 2) a decision on the intervention delivery format. To understand intervention users’ perspective of what might or might not be helpful in reducing stress, we will conduct ‘focus group discussions’ with 8–10 adolescents/ young adults to explore intervention formats (eg. smartphone-based) and content (eg. applied techniques) based on existing resources as means of support for managing stressful situations. Participants will also be invited to discuss their experiences of using any other resources.

A set of intervention materials will be produced based on the results of the above three steps.
**‘Think aloud’** interviews will be conducted where participants will be asked to verbalise their thoughts as they go through the intervention materials, which will identify features and technologies that they particularly enjoy and think they will use, and those that would irritate them
^56^. Materials will be adapted iteratively between interviews. In a longitudinal study, 5–10 young adults will be asked to use the intervention materials for several weeks before being interviewed about their experiences.

The final intervention design will incorporate the full range of techniques known to be effective, and identified by young adults as being acceptable, in reducing and helping to manage stress. The intervention module will be pilot tested in a future study.

### Data analysis

We will summarise repeated measures of cortisol and cardiovascular response to stress in a time weighted average (TWA). Linear and logistic regression models will be used to examine associations of stress responses (TWA) with risk outcomes (eg. blood pressure, depression). These models will be adjusted for age, sex, socio-economic status, and relevant maternal and offspring co-variates.

We will use linear mixed-model regression analysis to examine associations of maternal exposures with repeated measures of cortisol and cardiovascular parameters to account for within-group correlations.

We will use the conditional analysis method
^57^ to examine the change in stress responses from early adolescence to adulthood in Mysore, to explore tracking.

Metanalysis: We will also do metanalyses of data from Mysore, Mumbai and Pune components of the study on the association of stress responses with 1) maternal nutritional status and 2) offspring NCD risk markers.

Qualitative interviews: Transcripts from qualitative interviews and conversations will be subject to thematic analysis, using a standard thematic analysis methodology involving constant comparative methods.

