## Introduction

Psychological stress is an unpleasant subjective experience, caused by an awareness of situational demands exceeding an individual’s adaptive capacity
^1^. It has been identified as an important lifestyle risk factor for adult non-communicable disease (NCD)
^2^. During stress, the body triggers physiological changes through the actions of the hypothalamic-pituitary-adrenal (HPA) axis (and its end product cortisol) and the autonomic nervous system, to maintain homeostasis
^2^. It is suggested that repeated psychological stress induces dysregulated HPA axis activity and autonomic cardiovascular control, reflected in either exaggerated or blunted responses of these systems to acute stress. Over time, these abnormalities can provoke the cardiometabolic, neuroendocrine and immunological disorders responsible for NCDs. Studies have shown increased cardiovascular and mental health disorders in relation to abnormal stress responses
^3,
4^.

The “Developmental Origins of Health and Disease (DOHaD) hypothesis” proposes that variations in nutrition during foetal development influence individual’s susceptibility to adult NCDs
^5^. Both intra-uterine growth restriction (resulting in low birthweight), and accelerated growth caused by maternal gestational diabetes (GDM), increase the risk of NCDs
^6–
8^. This phenomenon is thought to reflect permanent effects (‘programming’) of unbalanced foetal nutrition on physiological systems
^9^. Recent evidence suggests that altered neuro-endocrine responses to stress may be a pathway linking early life nutrition to the development of NCDs in later life
^10^. Maternal nutrients, particularly those involved in the one-carbon metabolism are vital for many neuro-developmental processes, and their deficiencies may alter neuroendocrine structure and function
^11,
12^, impair HPA axis feedback systems
^13,
14^, and influence stress reactivity. A few studies in adults and children have found associations between lower birth weight (as a proxy for maternal undernutrition) and higher cortisol and cardio-sympathetic responses to stress
^15–
18^. However, relationships of maternal nutritional status and maternal hyperglycemia
*per se* with offspring stress responses are not known.

There is an escalating prevalence of NCDs in India; ~80 million people in the country are expected to develop type 2 diabetes by 2030
^19^, and the estimated prevalence of GDM is ~15% currently

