## Protocol

### Study sample

The “Stress Responses in Adolescence and Vulnerability to Adult Non-communicable disease (SRAVANA) study” will adopt a multi-centric approach, leveraging on the unique characteristics of three Indian birth cohorts to achieve specific, but complementary objectives.

**The Mysore Parthenon Cohort** was established at HMH in 1997–1998 to investigate the long-term effects of maternal GDM and nutritional status on offspring NCD risk
^30^. The cohort comprised 663 normal offspring of 830 women whose GDM status had been assessed; ≈6% of them were OGDM
^31^. Offspring follow-up continued every 6–12 months after birth for anthropometry, body composition, pubertal staging, cardiometabolic and cognitive assessments. The study showed high rates of low maternal B12 and vitamin D status, and GDM, suggesting that undernutrition and overnutrition co-exist in this transitioning population
^31–
33^. Offspring exposed to maternal GDM had greater adiposity, insulin resistance and systolic BP, and higher cardiovascular stress responses during adolescence than those of mothers with normal glucose tolerance
^27,
34^. Higher risk markers were also observed in relation to lower offspring birthweight and maternal nutritional imbalances (vitamin D, folate and homocysteine)
^32,
33,
35^.

The cohort participants are currently aged 20, and ≈85% of the original cohort are still being followed up (N=550). For the present study, we will measure NCD risk markers, chronic stress in the whole cohort, and acute stress responses in a subsample (N~250) who participated in earlier studies of stress reactivity at the age of 13.5 years
^27^. See below for a detailed description of these assessments.

**The Mumbai Maternal Nutrition Project** (MMNP or “Project SARAS”; ISRCTN 62811278) was a community-based randomised trial of nutritional supplementation for women living in urban slums, pre-conceptionally and throughout pregnancy

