^39^. The cohort members (N=557) were enrolled when they were ~16–18y old, and were randomised to receive either i) B12 2µg, ii) B12 2µg plus multiple micronutrients plus milk protein (MMN), or iii) placebo daily. The intervention is ongoing. We will recruit ~50 participants each from the intervention and placebo groups at 22–23y of age. We will measure NCD risk markers and stress responses. We will test the hypothesis that current micronutrient supplementation is associated with improved cortisol and cardiovascular responses to stress in young adults exposed to maternal nutritional deficiencies.

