### Sample size and power calculation

Mysore: The sample size of the Mysore study component is based on the previous stress-responses study carried out during 2011–2013 among the Parthenon cohort participants
^41^. The previous sample size was calculated based on the only available study in children on the association between birth weight and stress response
^15^. We estimated that our sample will have 80% power to detect an effect size of 2.9 nmol cortisol increase per kg increase in birth weight at 5% significance level. In the current study, we aim to follow-up all the children who had participated in the above study. This sample size will have 80% power at the 5% significance level to detect an association of 0.18 SD of a continuous outcome (eg. TWA salivary cortisol) per SD of an exposure (eg. birth weight).

Mumbai: The sample size calculation for the Mumbai component of the study is based on the Mysore sample size. The estimated sample size will be able to detect an association of 0.16 SD of a continuous outcome per SD of a continuous exposure, and will detect a difference in outcome of 0.23 SD between the intervention and the control arms.

Pune: As there are no earlier studies on the effect of current nutritional intervention on stress responses, we based the sample size for this study on the findings from comparison of effect size between the offspring of B12 deficient and normal B12 status mother. The estimated sample size will detect an association of 0.28 SD of a continuous outcome per SD of an exposure. The study will detect a difference of 0.56 SD in the outcome between the control and intervention group.

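### The plan treats both exaggerated and blunted stress responses as harmful, but names no term for Objective 2 that would detect a two-directional relation with risk

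*Protocol article*

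**What the plan says.** **Theory.** The Introduction says that repeated stress dysregulates the HPA axis and autonomic control, "reflected in either exaggerated or blunted responses of these systems to acute stress". It continues: "Over time, these abnormalities can provoke the cardiometabolic, neuroendocrine and immunological disorders responsible for NCDs". Both directions of abnormality are thus placed on the path to disease.

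**Analysis.** Objective 2 relates stress responses to psychological and cardiovascular risk markers. For this the Data analysis section states: "Linear and logistic regression models will be used to examine associations of stress responses (TWA) with risk outcomes". It lists adjustment covariates but not the form in which the response enters the model.

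**Size and planned effect.** In Mysore the plan measures "acute stress responses in a subsample (N~250) who participated in earlier studies of stress reactivity at the age of 13.5 years". The sample size section gives 80% power at the 5% level for 0.18 SD of outcome per SD of exposure. The Mumbai and Pune continuous effects take the same form (0.16 and 0.28 SD per SD).

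**Direction.** The Introduction reports "associations between lower birth weight (as a proxy for maternal undernutrition) and higher cortisol and cardio-sympathetic responses to stress". The Mysore sample size text says that the earlier sample had "80% power to detect an effect size of 2.9 nmol cortisol increase per kg increase in birth weight". Objective 3 speaks of reducing responses. The Mumbai hypothesis speaks of normalising them, especially in offspring of mothers with gestational diabetes. The Pune hypothesis is that "current micronutrient supplementation is associated with improved cortisol and cardiovascular responses to stress", with no direction given.

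**The concern.** If low and high responses both mark dysregulation, mean risk as a function of the response may fall and then rise. A single slope averages the two limbs, and to the extent that they cancel, a real relation appears as no association. Objective 2 could then report a null for the pattern that the Introduction describes. The planned effects do not guard against this, because each is the size of a straight slope.

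The wording on direction is a lesser matter with the same root. Where both ends can be abnormal, the reader needs to know which shift counts as improvement, and which sign of the birth weight association would count as the persistence that Objective 1 sets out to test.

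**Working it through.** **Inputs.** N=250 and 0.18 SD per SD come from the protocol. A two-sided 5% test is assumed, because sidedness is not stated. The curve's shape, its turning point and the distribution of the response are also assumptions, so a range is shown.

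**1. The plan's own figure.** Detectable slope = (1.96 + 0.84)/√250 = 0.177; by Fisher's z, tanh(2.80/√247) = 0.176. Power at 0.18 = Φ(atanh(0.18)·√247 − 1.96) = Φ(2.86 − 1.96) = 82%. The stated 80% reproduces, as power for a straight slope.

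**2. A curved effect of the same size.** Let the outcome be K(x − c)² plus noise, with x in SD units, c the turning point, and K set so that the multiple correlation is R = 0.18. For normal x, (x − c)² has variance 2 + 4c², of which a straight line captures 4c². The correlation visible to a linear term is therefore

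r = 0.18 × √[2c²/(1 + 2c²)].

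For c = 0.5: r = 0.18 × √(1/3) = 0.104, and power ≈ Φ(0.104 × √247 − 1.96) = Φ(−0.32) ≈ 37%. For c = 0, r = 0 and the linear test has nothing to find.

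**3. Simulation** (4,000 runs per setting, N=250, normal x):

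| Turning point, SD from mean | Linear term alone | Added quadratic term | Joint 2-df test |
|---|---|---|---|
| 0 | 7% | 80% | 71% |
| 0.25 | 17% | 75% | 72% |
| 0.5 | 37% | 63% | 71% |
| 1 | 63% | 37% | 72% |
| 1.5 | 74% | 22% | 72% |

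The linear column agrees with the formula in step 2.

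**4. Skewed predictor** (standardised log-normal, log-scale SD 0.5):

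| Turning point, SD from mean | Linear term alone | Added quadratic term | Joint 2-df test |
|---|---|---|---|
| −0.25 | 48% | 41% | 59% |
| 0 | 38% | 45% | 55% |
| +0.5 | 19% | 57% | 53% |

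**5. If the truth is a straight line at 0.18.** The linear test has 82% power and the joint test 74%. Replacing the slope test would therefore cost about 8 points. Reporting a non-linearity test beside it leaves the slope test as it is.

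These figures are for a continuous outcome without covariates. They do not carry over directly to the logistic models.

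**6. Birth weight sign.** The Introduction's statement rests on references 15–18, and the Mysore calculation on reference 15 alone. One gives higher cortisol at lower birth weight; the other gives cortisol rising with birth weight. Reference 15 lies inside the range cited for the opposite direction.

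**The case against.** Four objections have weight.

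*Functional form is unstated, not fixed.* A reader might infer that the plan fits only straight lines. The text does not say so. Linear and logistic regression are model classes that can carry quadratic, spline or categorical terms, and a condensed article often leaves this choice to the full plan, which is not shown. This stands. What remains is that the theory is two-directional while every effect size that the article commits to is a slope.

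*The U-shape is background, not a hypothesis.* The sentence is hedged, and the study's working direction is mostly that high is adverse: exaggerated responses after maternal gestational diabetes, and an overall aim of reducing responses. A slope suits that. This supports keeping the slope as the main test. It does not remove the reason to check for curvature.

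*The lowest power is a worst case.* The 7% needs a turning point at the mean of a symmetric predictor, and the documents give neither the turning point nor the distribution. The planned meta-analysis also helps. At a pooled N of about 650 (250 + 300 + 100), assuming the same curve at all sites, simulated linear power is 36%, 74%, 96% and 99% for turning points 0.25, 0.5, 1 and 1.5 SD away. Only the centred case stays near 7%.

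*The directions mostly agree.* 'Normalises' is compatible with 'reducing', because the group singled out is described as over-responding. Making reduction the only favourable direction would also contradict the premise that blunting is harmful. Of the aims, only 'improved' is left without a meaning.

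**Conclusion.** The point holds as a mismatch between stated theory and stated analysis, and as an inexpensive improvement. If the relation is curved with a multiple correlation of 0.18 at N=250, a slope alone detects it with between 7% and 74% power for a normal predictor, against 71–72% for the joint test; with a skewed predictor it is 19–48% against 53–59%. The advantage is large when the turning point is near the mean and gone by 1.5 SD. All of this rests on an assumed quadratic shape.

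Two stronger readings are not supported. The documents do not show that the planned models have almost no power for a two-directional pattern in general. Nor does the sign conflict invalidate the Mysore sample size: two-sided power does not depend on sign, and the figure for the current study, 0.18 SD per SD, carries none. The conflict is real, but the documents cannot show which statement is right.

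**What to change.** 1. In the Objective 2 models, keep the linear slope of the stress response as the main test. Prespecify a quadratic term or a 3-knot restricted cubic spline, and report the test of non-linearity beside the slope. If the full protocol or analysis plan already does this, one sentence in the Data analysis section is enough.
2. Check the cited source and reconcile the direction of the birth weight–cortisol association between the Introduction and the sample size section.
3. State in the Aims and objectives (Objective 4) and in the Pune part of the Study sample section what counts as an improved response.

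**Cost.** Item 1 adds one parameter and one reported test per model. With cortisol and six haemodynamic measures set against several risk markers, this adds to multiplicity, so the non-linearity tests should be labelled as supporting. Their own power also falls as the turning point moves away from the mean (80% down to 22% in the normal case), so a non-significant result would not establish linearity. Items 2 and 3 are wording and change no sample size.
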